### Sample size {14}

The sample size is based on the main outcome (malaria incidence in a cohort of children followed prospectively in the cluster’s core area for six months), an outcome chosen based on WHO’s PPC for endectocides. This sample size has been corrected for cluster effect following Hayes and Bennett formula for unmatched rates [56].

The magnitude (20% reduction) was selected based on WHO’s recommended PPC for endectocides [57]. Additionally, the results of the RIMDAMAL trial suggest that a 20% reduction in malaria incidence can be achieved using a dosing regimen with a similar cumulative dose [40], these results although not statistically significant do point towards an expected effect size.

The final sample size is dependent on the population distribution as identified in the demography protocol.

The number of children per cluster can vary in order to streamline the cluster generation once the demographic data is available. The power, significance level, and target effect size will remain unchanged. The final number of clusters depends on the cluster size (the number of children in the active pediatric cohort recruited in the core of all clusters).

The target number of children to be included in every cluster is defined by the expected enrollment rate and loss to follow-up rate. We have estimated these as 15% and 20% respectively. So, for a cluster size to be 24 i.e., 24 children in the cohort finishing the study, the cluster must include 35 eligible children in the beginning (35 eligible of which an estimated 5 [15%] do not consent, 30 consent, of which 6 [20%] are LFU)

The number of clusters required increases exponentially as the number of children per cluster (cluster size) decreases. This is particularly marked below 13 children per cluster. The number of children presented is the number of eligible children required at the beginning, not accounting for 15% non-consenting and up to 20% LFU.

Peak incidence age: < 5 years

Power: 80%

Significance level: 5%

Expected incidence in the control group (λ0): 4.20

Expected incidence in the intervention (λ1): 3.36

Incidence reduction: 20%

Optimal cluster size: 20 children (assuming 3 non-consenting and 3 LFU)

Follow-up time: 6 months starting post-community dosing

Coefficient of variation (km): 0.35

People treated per cluster: approximately 300

Optimal total clusters required: 159 clusters (53 per arm)

The final sample size may have to be adjusted as by the table below. However, the power and effect size will remain constant as does the ceiling of treatable adults (not to exceed 48,000 eligible adults).

**Table Tabd:** 

Total clusters needed	Total children eligible per cluster	Non-consenting 15%	Included	LFU 20%	Final size	Total children in clusters	Total children enrolled	Total children completing trial
147	35	5	30	6	24	5145	4373	3499
149	30	5	26	5	20	4470	3800	3040
153	25	4	21	4	17	3825	3251	2601
159	20	3	17	3	14	3180	2703	2162
174	15	2	13	3	10	2610	2219	1775
195	10	2	9	2	7	1950	1658	1326
291	5	1	4	1	3	1455	1237	989

#### Preliminary data

The baseline incidence and the coefficient of variation used for the sample size calculation for Mozambique are considered robust as they have been obtained from a recently finished cluster-randomized trial in Mopeia, the very same district where BOHEMIA will be conducted. The previous trial assessed the cost-effectiveness of combining LLIN and IRS [58].

#### Calculations

Based on the demographic data to be confirmed in the preceding census, the clusters are planned to include approximately 420 people, of which 280 will be above 4–5 years of age and potentially eligible for treatment and 140 will be children under 5 potentially eligible for follow-up. There will be 53 clusters per arm in Mozambique.

Clusters in Mozambique will be randomized in three arms, resulting in inclusion of approximately 45,000 participants to receive treatment or control and approximately 2000–4000 children to be followed for 6 months.

With this sample size, the study has 80% power at 5% significance to detect a 20% reduction in malaria incidence infection, from 4.20 cases/child-year at risk to 3.36 for the human-only intervention, using a coefficient of variation (km) of 0.35 for Mopeia/Mozambique. This value for km has been back-calculated from a cluster randomized trial recently conducted in the same study site [58].

For the human and livestock intervention, this sample size has 80% power to detect a further 20.5% reduction in malaria incidence infection between the human and human + livestock intervention arms, from 3.36 cases/child-year at risk (the lower incidence expected in the human only arm) to 2.67.

The total number of clusters needed per arm has been increased by one for all scenarios to account for potential LFU of a whole cluster (withdrawal of community consent, displacement, etc.)

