## Assignment of interventions: allocation

### Sequence generation {16a}

Once all clusters in the district are defined, the target sample will be randomized using a computer-generated algorithm. Clusters will be randomized 1:1:1 into three study arms. The treatment status of each cluster will be assigned during cluster delineation and then transmitted to the population during a randomization ceremony

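### The sample-size table does not show the extra cluster per arm that the protocol says was added in every scenario, and its 149-cluster row cannot be split equally over three arms (minor)

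*Protocol article*

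**What the plan says.** Sample size {14} names the method: "This sample size has been corrected for cluster effect following Hayes and Bennett formula for unmatched rates". It lists the inputs: power 80%, "Significance level: 5"%, "Expected incidence in the control group (λ0): 4.20", "Expected incidence in the intervention (λ1): 3.36", "Coefficient of variation (km): 0.35", and six months of follow-up. The chosen scenario is 20 eligible children per cluster, and the result is "Optimal total clusters required: 159 clusters (53 per arm").

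A table then gives seven scenarios, from 147 clusters with 24 completing children each to 291 clusters with 3. The text just before it allows the final size to move along this table while power and effect size stay fixed.

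Calculations repeats 53 clusters per arm and adds: "The total number of clusters needed per arm has been increased by one for all scenarios to account for potential LFU of a whole cluster". The causes it has in mind include withdrawal of community consent and displacement. Sequence generation {16a} states: "Clusters will be randomized 1:1:1 into three study arms".

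**The concern.** If one cluster per arm had been added in every scenario, each table total should exceed the formula's requirement by three, and every total should divide by three. Neither holds. A reader of Calculations would conclude that the design keeps its 80% power after a whole cluster drops out of each arm, whereas the 53 per arm appears to be the requirement itself.

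Such a loss was plausible: the Discussion reports cyclones, flooding and a cholera outbreak, and Trial status adds rumours. The table is also the stated means of resizing the trial at constant power, so its rows should be built by one rule.

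**Working it through.** **Inputs.** All are from Sample size {14}: λ0 = 4.20 and λ1 = 3.36 per child-year, km = 0.35, power 80%, significance 5%. Sidedness is not stated; two-sided is assumed, so z = 1.960 and 0.842, and (1.960 + 0.842)² = 7.849. Child-years per cluster are y = Final size × 0.5, using the table's Final size column (completers).

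**Formula** (Hayes and Bennett, unmatched rates), per arm:

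c = 1 + 7.849 × [(λ0 + λ1)/y + km²(λ0² + λ1²)] / (λ0 − λ1)²

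The leading 1 belongs to the formula. It compensates for using normal quantiles with a limited number of clusters and is not a loss allowance.

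**Reproducing the chosen scenario.** Final size 14, so y = 7.
- (λ0 + λ1)/y = 7.56/7 = 1.080
- km²(λ0² + λ1²) = 0.1225 × (17.64 + 11.29) = 3.544
- (λ0 − λ1)² = 0.84² = 0.7056
- c = 1 + 7.849 × 4.624/0.7056 = 1 + 51.43 = 52.43, rounded up to 53 per arm, or 159 in total

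The plan's figure is reproduced exactly, with no further cluster added.

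**All rows.**

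| Final size | Formula c | Rounded up | Total, no reserve | Total, +1 per arm | Table total | Table ÷ 3 |
|---|---|---|---|---|---|---|
| 24 | 47.43 | 48 | 144 | 147 | 147 | 49 |
| 20 | 48.83 | 49 | 147 | 150 | 149 | 49.67 |
| 17 | 50.31 | 51 | 153 | 156 | 153 | 51 |
| 14 | 52.43 | 53 | 159 | 162 | 159 | 53 |
| 10 | 57.24 | 58 | 174 | 177 | 174 | 58 |
| 7 | 64.45 | 65 | 195 | 198 | 195 | 65 |
| 3 | 96.48 | 97 | 291 | 294 | 291 | 97 |

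The last five rows equal the formula without a reserve. The first row equals the formula plus one per arm. The second equals neither and does not divide by three.

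**Power at the chosen size.** Inverting the formula, power = Φ(√((c − 1)/V) − 1.960), with V = 4.624/0.7056 = 6.553.
- c = 53: √(52/6.553) = 2.817; Φ(0.857) = 80.4%
- c = 52: √(51/6.553) = 2.790; Φ(0.830) = 79.7%

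For the second contrast in Calculations (3.36 vs 2.67) the formula gives 52.40, again 53 per arm. Power is 80.5% at 53 and 79.7% at 52.

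**The case against.** **The formula's '+1' may be what was meant as the reserve.** The article names the formula but does not print it. Without the leading 1 the requirement rounds up to 47, 48, 50, 52, 57, 64 and 96 per arm, and adding one gives the same five table rows, including 53. That reading is possible. It does not rescue the sentence: the 147 row would then carry two extra clusters per arm and the 149 row 1.67, and a term of the cited formula would be missing.

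**Rounding to the nearest whole number** also turns 52.43 + 1 = 53.43 into 53. The same rule would give 48 and 50 per arm in the first two rows (144 and 150), not 147 and 149, and losing one cluster from 53 leaves 52, below the 52.43 required.

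**The 79.7% is conservative.** It gives no time to children lost to follow-up, although they contribute visits before leaving. If the 3 lost children per cluster are assumed to contribute half their follow-up, y = 7 + 3 × 0.25 = 7.75, and power is 81.3% at 53 and 80.6% at 52. This stands, so 80% is roughly kept after such a loss.

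**The 149 row was not chosen,** and Trial status reports recruitment complete in July 2022. It can no longer drive an allocation. It remains an error in the table.

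**A stronger reading is tempting:** that true power is only 78–79%, because 14 days at risk are lost after each treatment. The document does not support this as headline power. Efficacy analysis counts each RDT as one child-month at risk and mentions the 14-day deduction only for the per-protocol correction. Crediting full months in the sample size agrees with that counting rule.

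**Conclusion.** The statement that one cluster per arm was added in all scenarios does not match the table on any of the readings examined. On the cited formula as it stands, the chosen 53 per arm and four other rows have no reserve, one row has a full reserve, and the 149 row fits neither rule and cannot be randomised 1:1:1.

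The size is minor. A consistent reserve would have meant 162 clusters instead of 159, and losing one cluster per arm costs about 0.7 percentage points, ending about 0.3 points below the nominal 80% (completers only) or slightly above it if partial follow-up counts. A reader might infer that the trial is materially underpowered; these figures do not show that.

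The result rests on two-sided 5%, on the Final size column as the number of children contributing six months each, and on rounding up per arm. That these choices reproduce five rows exactly supports them but does not prove how the table was built.

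**What to change.** Correct the text and table in one of two ways.
- **No reserve:** delete the loss-allowance sentence, or say that the one added cluster is the formula's own term. The totals become 144, 147, 153, 159, 174, 195 and 291.
- **With reserve:** keep the sentence and apply it to every row. The totals become 147, 150, 156, 162, 177, 198 and 294.

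Either way 149 goes, replaced by 147 or 150, and the first row follows the same rule.

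For the fielded 159 clusters, state power of about 80.4% with no cluster lost and about 79.7% if one per arm is lost, counting completers only, and note that it is slightly higher if children lost to follow-up contribute time. Any figure using the 14-day deduction should be at most a sensitivity figure for the per-protocol correction.

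The cost is a wording and table correction. No enrolment, allocation or analysis changes; the only loss is a claim of protection that the chosen size does not fully provide.

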### Recruitment {15}

Community mobilization teams will visit all villages and meet with leaders and community members to inform them of the upcoming trials. The information methods will include door-to-door visits and focal group discussions (see stand-alone community mobilization plan)

## Assignment of interventions: allocation

### Sequence generation {16a}

Once all clusters in the district are defined, the target sample will be randomized using a computer-generated algorithm. Clusters will be randomized 1:1:1 into three study arms. The treatment status of each cluster will be assigned during cluster delineation and then transmitted to the population during a randomization ceremony

### Concealment mechanism {16b}

The sequence will be encrypted and the password kept by an independent data manager

### Implementation {16c}

The sequence was generated by an independent data manager. Recruitment is carried on by unblinded field workers

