### Who will take informed consent? {26a}

Appropriately trained and qualified field workers will visit the selected households and explain the study objectives, methods, and procedures to all household members who will be invited to participate in the study. The field workers will explain the inclusion and exclusion criteria and offer to answer questions as part of the informed consent process.

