**Table Tabc:** 

Procedures in efficacy (active pediatric cohort)	Census and clustering Months −10 to −4	Enrollment/baseline(E) Visit 1, day 1	Study visit 2(E) Day 31 +/−3 days	Study visit 3(E) Day 61 +/− 3 days	Study visit 4(E) Day 91 +/−3 days	Study visit 5(E) Day 121 +/−3 days	Study visit 6(E) Day 151 +/−3 days	Study visit 7(E) Day 181 +/−3 days
Informed consent for census	X							
Demographic data collection	X							
Randomization	X							
Informed consent		X						
Anthropometry		X			X			X
Review infant vaccination card		X			X			X
Complete visit template		X	X	X	X	X	X	X
Malaria RDT		X	X	X	X	X	X	X
Malaria treatment ^a^		X	X	X	X	X	X	X
Assessment of selected NTDs		X	X	X	X	X	X	X
COVID response^b^		X	X	X	X	X	X	X
Malaria parasite immune response samples ^b^		X	X	X	X	X	X	X
*Plasmodium* PCR for quality control and molFOI^c^		X	X	X	X	X	X	X
Passive incidence surveillance at health facilities (all ages)		X-------------------------------------------------------X						

^a^Only if RDT is positive (see case definition)

^b^Only in a randomly selected sub-sample

^c^Only in a randomly selected 10% sub-sample

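### Cohort children are enrolled after allocation by unblinded field workers, and the stated analysis only partly guards against selective enrolment by arm

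*Protocol article*

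**What the plan says.** **Order of events.** In the active paediatric cohort table of Participant timeline {13}, randomization is ticked under "Census and clustering Months −10 to −4". Informed consent for the cohort is ticked under "Enrollment/baseline(E) Visit 1, day 1".

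**Who enrols.** Implementation {16c} states: "Recruitment is carried on by unblinded field workers". The consent section {26a} adds: "Appropriately trained and qualified field workers will visit the selected households".

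**When clusters are allocated and who is told.** Sequence generation {16a} opens with "Once all clusters in the district are defined, the target sample will be randomized". Two sentences later it says: "The treatment status of each cluster will be assigned during cluster delineation and then transmitted to the population during a randomization ceremony".

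**Safeguards stated.** Concealment mechanism {16b} says: "The sequence will be encrypted and the password kept by an independent data manager". Who will be blinded {17a} describes outcome assessors as blinded. Statistical methods {20a} plans a comparison of baseline characteristics between groups. The Efficacy analysis section plans a GEE count model and an adjusted model. Its candidate covariates are demographic (including age), socio-economic and clinical, and they are chosen stepwise from those with univariate p below 0.20. That section also compares children who remain with those lost to follow-up.

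**The concern.** In a cluster trial, concealing the sequence protects the assignment of clusters. It does not protect the later step that decides which individuals enter the denominator. Here that step follows allocation and is carried out by staff who know the arm. If persuasion, approach or refusal differs by arm in a way related to malaria risk, the enrolled children differ in expected incidence before any drug effect. Blinded outcome assessment cannot undo this. The cluster-robust standard error in a GEE allows for correlation within clusters, not for a shift in who was enrolled.

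The target effect is a 20% reduction, so a shift of several percent in one arm matters. It could create part of an apparent effect or hide part of a real one.

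The timing conflict in {16a} raises a separate question. If status was assigned while clusters were still being drawn, borders and cores could have been set with the arm known.

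**Working it through.** **1. The plan's own figure.** Inputs from Sample size {14}: rates 4.20 and 3.36 per child-year, km 0.35, power 80%, significance 5% (two-sided assumed), 14 children completing per cluster, follow-up 0.5 year. So y = 14 × 0.5 = 7 child-years per cluster.

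Hayes–Bennett, unmatched rates: c = 1 + (z_α/2 + z_β)² × [(λ0 + λ1)/y + km²(λ0² + λ1²)] / (λ0 − λ1)²

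- (1.96 + 0.8416)² = 7.849
- (4.20 + 3.36)/7 = 1.08
- 0.1225 × (17.64 + 11.29) = 3.544
- (4.20 − 3.36)² = 0.7056
- 7.849 × 4.624/0.7056 = 51.43; adding 1 gives 52.43, rounded up to 53 per arm, 159 in total

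This reproduces the stated 159.

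**2. Smallest significant reduction.** With 80% power for a 20% reduction, the observed reduction that just reaches two-sided 5% is about 20% × 1.96/(1.96 + 0.84) = 14%.

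**3. Illustrative selection.** The 15% non-consent comes from the document. Two things are assumed: refusers in one arm have r times the average incidence, and refusal in the comparison arm is unrelated to risk. Enrolled mean relative to eligible mean = (1 − 0.15r)/0.85.

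| r (assumed) | Ratio | Shift in that arm |
|---|---|---|
| 1.3 | 0.805/0.85 = 0.947 | 5.3% lower |
| 1.5 | 0.775/0.85 = 0.912 | 8.8% lower |

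**4. Effect on the test.** The standard error has the same form as in step 1, with 51 effective clusters per arm (53, less the formula's added cluster, less one allowed as lost).

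| Ratio in affected arm | Rejection rate, no true effect, selection in an intervention arm | Power for a true 20% reduction, selection in control |
|---|---|---|
| 1.000 | 5% | about 80% |
| 0.947 | about 11% | about 56% |
| 0.912 | about 22% | about 37% |

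For the second row of the rejection column (ratio 0.947): the shifted rate is 4.20 × 0.947 = 3.98, the difference 0.222, the standard error 0.321, and their ratio 0.69. The two-sided rejection probability is then about 0.106.

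**5. Do the stated checks see this?**

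| Stated check | What it covers | What it leaves |
|---|---|---|
| Baseline comparison {20a} | Enrolled children, measured factors | Children listed but not enrolled |
| Adjusted model | Listed covariates passing p<0.20 | Day-1 RDT is not listed; age may drop out |
| Remaining versus lost to follow-up | Attrition | Enrolment |
| Encrypted sequence {16b} | Cluster assignment | Individual enrolment |

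The schedule gives every cohort child an RDT at Day 1, so the most direct baseline marker of infection risk is collected but is missing from the covariate list.

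**The case against.** The strongest reply is that the plan does not leave this bias unexamined. It has a baseline comparison, a Day-1 RDT and an adjusted model covering age, net use and socio-economic factors. That stands: the protection is partial, not absent.

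Four stronger readings are tempting, and the document does not support them.

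- **Staff could choose about 20 children from about 140.** The 140 under-fives in Calculations are a whole-cluster count, while the cohort is recruited in the core, whose under-five count is not given. The sample size table takes 159 × 20 = 3180 children and removes only non-consent and loss to follow-up, with no sampling step.
- **Borders were drawn with the arm known.** The first sentence of {16a} gives the opposite order. The later mention of delineation may name only the study phase, since the schedule puts clustering and randomization in one column. This is wording to reconcile, not evidence that allocation came first.
- **Parents knew the arm when they consented.** The public ceremony makes this plausible, but its date is not given, and {17a} says participants are told they receive one of two anthelminthics.
- **The recruitment sentence is about the cohort specifically.** It does not single the cohort out. That it includes the cohort is the natural reading, but an inference.

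It is also fair that the illustrated shift rests on assumed risk ratios and on selection in one arm only, and that it stays below the 14% threshold. Step 4 shows it can still matter, because it adds to chance variation. Finally, the SAP is not shown and may contain further safeguards. The point concerns what the article itself fixes: a covariate list and a selection rule.

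**Conclusion.** The concern holds in a limited form. Cohort enrolment follows allocation, recruitment is by unblinded staff, and the stated analysis guards only partly against selective enrolment by arm. The document does not show that selection occurred, in either direction. Under the stated 15% refusal and the assumed r of 1.3 to 1.5 in one arm, enrolled incidence there falls by 5% to 9%. That would raise the false-positive rate from 5% to roughly 11% to 22%, or, if it occurred in control, cut power from about 80% to roughly 56% to 37%. These are illustrations of scale, not estimates. The two statements on when clusters were allocated in {16a} need to be reconciled whatever the size of the bias.

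**What to change.** Before unblinding:

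1. Prespecify the Day-1 RDT result and age as fixed covariates in the primary GEE, in place of the p<0.20 stepwise rule for these two variables. If the SAP already does this, align the article's text with it.
2. Report by arm the census-listed under-fives in the core against those enrolled, with baseline RDT positivity. Add refusals only if they were logged; the document does not say that they were.
3. Reword Sequence generation {16a} to give one time for allocation, and state whether cluster borders and cores were frozen before allocation was released.

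The cost is slight extra analysis work, one table and a wording change. Background {6a} says the analysis team was still blinded at submission, so the covariates can be fixed without sight of results by arm. The limit is that adjustment corrects only measured differences; the listed-versus-enrolled table shows how much room remains for the rest.

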## Assignment of interventions: blinding

### Who will be blinded {17a}

The study will be open-label but outcome assessor-blinded participants in the ivermectin and control arms will receive products that differ in aspect and numbers. Participants will be informed that they are taking one of two anthelminthics. The sponsor and the study statistician will remain blinded to the assignment of each cluster group. All unblinded DSMB reports will be prepared by an independent statistician

